		Satisfied	
3.	To what extent do you find the chewing ability of your denture satisfactory?	Dissatisfied	
		Neutral	
		Satisfied	
4.	To what extent are you happy with the comfort of your new denture?	Dissatisfied	
		Neutral	
		Satisfied	
5.	To what extent do you find the speech and sound produced by the denture satisfactory?	Dissatisfied	
		Neutral	
		Satisfied	
6.	How satisfied are you with the way your dentures fit and removal?	Dissatisfied	
		Neutral	
		Satisfied	
7.	Does your denture harm the soft tissues in any way?	Yes	
		No	
8.	Do you have any issues with swallowing because of the denture?	Yes	
		No	

**Table 3 TAB3:** Questionnaire 2 (after seven days of denture insertion) Reference: [1,6,7]

Sr. No.	Questions	Options	No. of Patients
1.	To what extent are you satisfied with the adhesive's ability to keep your upper denture in place?	Dissatisfied	
		Neutral	
		Satisfied	
2.	To what extent are you satisfied with the adhesive's ability to keep your lower denture in place?	Dissatisfied	
		Neutral	
		Satisfied	
3.	How was your chewing experience after using this denture adhesive?	Worse	
		No difference	
		Better	
4.	For what duration did the denture adhesive work on your dentures?	≤4 hours	
		4-8 hours	
		8-12 hours	
5.	How does this denture adhesive taste?	Bad	
		Neither good nor bad	
		Good	
6.	How did you find it to remove the adhesive from your dentures?	Difficult	
		Neutral	
		Easy	
7.	How did you find it difficult to clean your denture after using the denture adhesive?	Difficult	
		Neutral	
		Easy	
8.	How difficult was it for you to wipe your oral cavity after using the denture adhesive?	Difficult	
		Neutral	
		Easy	

Sample Size

The sample size is determined using the following formula: n = {(Z 1-α/2 + Z 1-β)2 p1(1-p1) + p2 (1-p2)}/(p1-p2)^2^, where the proportion of outcome from group 1 (p1) = 0.37, the proportion of outcome from group 2 (p2) = 0.22, the level of significance (α) = 0.05, power (1-β) = 0.80, Z alpha value = 1.96, Z beta value = 0.84, and the total sample size = 40. The sample size estimation is done at a 95% confidence interval. Each group consists of 20 samples.

Statistical analysis

The statistical analysis will be done using IBM SPSS Statistics for Windows, Version 23 (Released 2015; IBM Corp., Armonk, New York). Descriptive statistics will be used for the mean distribution of both groups, and an independent sample t-test will be used for intergroup analysis between both groups.

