Age will be given using mean and standard deviation; however, frequency percentage will be used for qualitative characteristics. The independent t-test will be used to compare age between the two groups, and the Pearson chi-square test or Fisher's exact test will be used to compare all qualitative variables at a significant level of p-value ≤0.05 for all variables. The total of each questionnaire's scores will be used to determine the overall satisfaction with the results. Next, choose the percentage of satisfaction for every patient in both groups. The Wilcoxon signed-rank test will be used to compare patient satisfaction before and after the interview.

Ethical considerations

This study has been approved by the Institutional Ethics Committee of Datta Meghe Institute of Higher Education and Research (DMIHER(DU)/IEC/2024/56) dated May 11, 2024. Participant confidentiality will be maintained, and all procedures will adhere to ethical guidelines for research.

Trial registration

The study is registered with the Clinical Trial Registry-India under the CTRI Registration number CTRI/2024/06/068933, registered on June 14, 2024.

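### Ordered three-level questionnaire answers are compared between groups with tests that ignore the order, a second test can be applied to the same items, and the satisfaction score has no assigned between-group test

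*Protocol article*

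**What the plan says.** The Statistical analysis part of Materials and methods has two paragraphs that bear on the comparison of the two adhesives.

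- The first says "Descriptive statistics will be used for the mean distribution of both groups" and then that "an independent sample t-test will be used for intergroup analysis between both groups". It names no variable.
- The second says "The independent t-test will be used to compare age between the two groups", and that "the Pearson chi-square test or Fisher's exact test will be used to compare all qualitative variables", with significance at p ≤ 0.05 for every variable.
- On the score it says "The total of each questionnaire's scores will be used to determine the overall satisfaction with the results", followed by a percentage of satisfaction for each patient. The only test named for satisfaction as such is within patients: "The Wilcoxon signed-rank test will be used to compare patient satisfaction before and after the interview".

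Table 3 (Questionnaire 2) holds eight items, each with three ordered answers. One is "To what extent are you satisfied with the adhesive's ability to keep your lower denture in place", answered Dissatisfied, Neutral or Satisfied. In Table 2 (Questionnaire 1) six items are ordered in three levels and two are Yes/No.

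The Sample Size part works from a binary proportion, 0.37 versus 0.22, with 20 patients per group.

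**The concern.** The answers in Table 3 are qualitative, so the second paragraph sends them to chi-square or Fisher. They are also what the groups are compared on, so the unrestricted t-test sentence can be read to cover them too. Two things follow.

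First, the unordered test treats three ranked answers as three unrelated labels. If one adhesive moves patients up the scale, a test that uses the order will usually detect this more often, and a 40-patient trial has little power to spare.

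Second, where two stated rules both fit the same item, the analyst could pick the smaller p-value after seeing the data.

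The total or percentage score, which the plan uses for overall satisfaction, has the opposite gap: no between-group test is assigned to it.

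**Working it through.** **The plan's own figure.** The plan gives no power for any of these tests; its only related figure is N = 40. With brackets as evidently intended, the Sample Size formula gives (1.96 + 0.84)² × (0.37 × 0.63 + 0.22 × 0.78) / (0.37 − 0.22)² = 7.84 × (0.2331 + 0.1716) / 0.0225 = 141.02 per group. As literally printed it gives (7.84 × 0.2331 + 0.1716) / 0.0225 = 88.85. Neither gives 20 per group. That is a separate and larger problem. Here it matters only because n = 20 per arm is what the trial will have.

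**Inputs.** From the protocol: 20 per arm, two-sided p ≤ 0.05, three ordered levels, planned proportions 0.22 and 0.37. Assumed, because the protocol gives none: the three-level response distributions.

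**Method.** Each arm has 22 × 21 / 2 = 231 possible three-level tables, so 231² = 53,361 pairs were enumerated exactly. For each pair:
- Pearson chi-square: X² = Σ(O − E)²/E, 2 df when all three levels occur.
- Rank-sum: z = (U − 200)/√V, with V = (400/12) × [41 − Σ(t³ − t)/(40 × 39)] and t the column totals.
- t-test on scores 1-2-3, pooled variance, 38 df.

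**One table by hand.** Assume counts 10/6/4 in one arm and 4/6/10 in the other; column totals are 14/12/14.
- Chi-square: 4 × 3²/7 = 5.14, p = exp(−2.57) = 0.076.
- Rank-sum: U = 6 × 10 + 10 × 16 + ½(40 + 36 + 40) = 278. V = 33.33 × (41 − 7176/1560) = 1213.3. z = 78/34.83 = 2.24, p = 0.025.
- t-test: means 1.7 and 2.3, variance 12.2/19 = 0.642 in each arm. t = 0.6/√(0.642 × 2/20) = 2.37, p about 0.02.

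The same data are non-significant under one stated rule and significant under the other.

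**Type I error.** Control distributions (Dissatisfied/Neutral/Satisfied) 20/30/50, 33/34/33 and 40/35/25, no true difference: chi-square 5.0%, rank-sum 4.9%, t-test 5.1-5.2%. With 80% in the top category, chi-square falls to about 3%, which is conservative.

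**Choosing after the fact.** Under the null, chi-square and the t-test disagree on significance in 5.1% of trials. P(either significant) = [P(chi-square) + P(t) + P(disagree)]/2 = (5.0 + 5.1 + 5.1)/2 = 7.6% per item.

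**Power when the shift is in one direction:**

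| Scenario | Chi-square | Rank-sum | Loss (points) |
|---|---|---|---|
| Top category 22% vs 37%, proportional odds (OR 2.08), three control distributions | 16-18% | 21-23% | 5-6 |
| 0.4 SD latent shift | 14-15% | 18-20% | 4-5 |
| 0.8 SD, controls in the order above | 40 / 47 / 49% | 52 / 58 / 59% | 10-12 |
| 1.0 SD, same order | 55 / 66 / 68% | 68 / 76 / 78% | 10-13 |

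On the latent-normal scale, 22% versus 37% is −0.33 − (−0.77) = 0.44 SD, so the last two rows describe effects about twice the planned one. The t-test on 1-2-3 scores is within about 2.5 points of the rank-sum test in every proportional-odds scenario examined.

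**Power when the shift is not uniform:**

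| Control vs other arm | Chi-square | Rank-sum |
|---|---|---|
| 5/65/30 vs 5/30/65 | 54% | 55% |
| 40/40/20 vs 10/70/20 | 55% | 31% |
| 20/60/20 vs 20/20/60 | 75% | 48% |

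**The case against.** The strongest reply is that the two paragraphs can be read together without conflict: the t-test for quantities with means (age and the total or percentage score), chi-square or Fisher for single items. The t-test sentence follows one about means, and the age sentence does not say that the t-test is for age only. A reader might infer that the plan contradicts itself; the text does not establish that. But the reconciling reading is not written down either. The t-test sentence has no variable, and the score has no between-group test, so the overlap and the gap both stand.

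A reader might also infer that both tests mishandle the answers. That fails. The t-test on 1-2-3 scores uses the order, keeps type I error near 5% and nearly matches the rank-sum test in power; its price is the assumption of equal spacing. Chi-square and Fisher are valid too. What remains is efficiency, not error.

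Nor is there a fixed loss of about 10 points. That size belongs to shifts about twice the planned effect, and the sign reverses under some non-uniform shifts.

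Finally, it is tempting to say that chi-square leaves the direction unknown. The plan reports frequency percentages, which show it; the test itself is simply not directed at it.

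**Conclusion.** The point holds as one of unassigned and inefficient between-group tests, not as a contradiction or an invalid analysis. The ordered items go to a test that ignores their order, a second stated test can be applied to the same items, and the satisfaction score has none.

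The free choice between chi-square and t-test is worth about 2.6 percentage points of extra false positives per item (7.6% against 5.0%), if the analyst always reports whichever is significant. The power given up is about 4-6 points near the planned effect and about 10-13 points at 0.8-1.0 SD. These figures assume 20 per arm, a shift in one direction and the response distributions listed; the protocol supplies no distribution against which to check them.

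Changing the test does not rescue the sample size: at the planned proportions power moves only from 16-18% to 21-23%. The change is worth making because it is cheap and closes the choice before data are seen.

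**What to change.** State in the Statistical analysis section, before any outcome data are examined:

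- Each ordered three-level item is compared between groups with the tie-corrected Wilcoxon rank-sum (Mann-Whitney) test, or a proportional-odds model, and reported with an effect estimate (probability of a better response, or common odds ratio) and 95% CI.
- The total or percentage satisfaction score is compared between groups with one named test, either the t-test or the rank-sum test.
- The t-test stays for age. Chi-square or Fisher's exact test stays for nominal and Yes/No variables; the Yes/No questionnaire items occur only in Questionnaire 1.
- The unrestricted t-test sentence is limited to the variables it is meant for.

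This costs wording only: no patients, visits or data are added. The downside is statistical. If the effect is not a shift in one direction, for example Dissatisfied to Neutral with no gain in Satisfied, the rank test has less power than chi-square (31% against 55% in the example above). The change also does not say which of the eight items is primary; that needs its own sentence.

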Denture adhesives are categorized based on their forms, such as powder, tapes, gels, and paste. Denture adhesive enhances retention, lessens denture soreness, avoids strangling the mucosal blood supply, and lessens the need for adjustments even when the denture fits [4]. Additionally, there have been reports of improvements in biting force and chewing efficiency, which lead to a wider dispersion of occlusal forces over the tissues supporting the denture and a decrease in local pressure. The lubricating and cushioning properties of adhesives lessen friction and discomfort in the mucosa. Denture adhesives can be very beneficial for patients with muscle control deficiencies caused by hormonal or neurotransmitter abnormalities [5]. This study aims to evaluate and compare two different types of commercially available herbal denture adhesives with regard to patient satisfaction with denture retention.

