## Materials and methods

Method

This experimental study will be conducted in the Department of Prosthodontics, Sharad Pawar Dental College and Hospital, Sawangi (M), Wardha, India. The data will be collected in the postgraduate clinic of the Department of Prosthodontics. On the basis of the inclusion and exclusion criteria (Table 1), the patients will be divided randomly into two groups: Group A (n=20) (herbal denture adhesive without essential oil) and Group B (n=20) (herbal denture adhesive with essential oil). A total of 16 closed-ended questions will be asked of patients: eight during denture insertion without using denture adhesives and eight questions seven days after using denture adhesives.

**Table 1 TAB1:** Inclusion and exclusion criteria

Inclusion Criteria	Exclusion Criteria
Patients who are first-time denture wearers	Patients with tooth-supported overdentures
Patients who are old complete denture wearers	Patients with implant-supported overdentures
Patients who are willing to participate in the study	Patients with a single complete denture

The denture adhesive will be fabricated by utilizing carboxymethylcellulose with flavor, mineral oil, petroleum, silica particles, and mesoporous nanoparticles of the selected essential oil (cinnamon oil) with antimicrobial action incorporated into a gel for prolonged release, giving better effectiveness. In order to gather information about denture fitting, removal, chewing, retention, and phonetics, a standard questionnaire form will be given to each patient. Following the patient's answer to Questionnaire 1 (Table 2), a clinical examination and application of denture adhesive demonstration will take place, adhering to the guidelines provided by the manufacturer. The patients will be provided with an explanation of the cleaning routine and the administration of denture adhesive for the next seven days. The patients will be contacted back a week later to complete an additional questionnaire (Table 3) in which they will be asked to rate the denture's strength, biocompatibility, convenience, and masticatory abilities using the glue that was provided.

**Table 2 TAB2:** Questionnaire 1 (at the time of denture insertion) Reference: [1,6,7]

Sr. No.	Questions	Options	No. of Patients
1.	To what extent do you find the retention of your upper denture satisfactory?	Dissatisfied	
		Neutral	
		Satisfied	
2.	To what extent do you find the retention of your lower denture satisfactory?	Dissatisfied	
		Neutral	

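### The aim is satisfaction with retention, but every qualitative variable is tested at p ≤ 0.05 with no lead comparison, and the questionnaire total cannot stand in for retention

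*Protocol article*

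**What the plan says.** The Introduction closes with a single aim: to compare the two adhesives "with regard to patient satisfaction with denture retention".

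The Methods describe 16 closed-ended questions, "eight during denture insertion without using denture adhesives and eight questions seven days after using denture adhesives". The second set is Questionnaire 2 (Table 3), in which every item has three response options.

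The Statistical analysis section then lists several tests and ranks none of them:

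- For categorical data, a chi-square or Fisher test whose stated task is to "compare all qualitative variables at a significant level of p-value ≤0.05 for all variables".
- For means, "an independent sample t-test will be used for intergroup analysis between both groups"; the variable is not named.
- For a summary score, "The total of each questionnaire's scores will be used to determine the overall satisfaction with the results".
- For change over time, a Wilcoxon signed-rank test of satisfaction before and after.

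The Sample Size section uses proportions of 0.37 and 0.22 for an outcome that it does not name. The Abstract's expected results put overall satisfaction first, then mention stability, hold of the lower denture, chewing and patient satisfaction.

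**The concern.** A trial with one stated aim should make clear which single result answers it. Here at least three candidates compete: satisfaction with retention (Introduction), overall satisfaction as a questionnaire total (Abstract and Statistical analysis), and the unnamed proportion behind the sample size. The one decision rule that is stated gives every qualitative variable the same 0.05 threshold.

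If the items disagree, nothing in the text says which one decides, so any item that reaches 0.05 could become the headline. Disagreement is a realistic prospect. The Discussion describes a similar seven-day comparison of two adhesives in which lower-denture retention and duration of adhesion improved significantly, while upper-denture retention and ease of removal did not. The Results section is also already worded in favour of the essential-oil product.

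The total might seem to settle the matter, but most of what it adds up is not satisfaction with retention.

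**Working it through.** **The plan's own figures.** The only error rate stated is α = 0.05; no rate is given for the set of tests as a whole. The stated sample size does not reproduce. With p1 = 0.37, p2 = 0.22, Z values 1.96 and 0.84 and the usual bracketing, (1.96 + 0.84)² × (0.37 × 0.63 + 0.22 × 0.78) / 0.15² = 7.84 × 0.4047 / 0.0225 = 141 per group. Bracketed exactly as printed, the formula gives 88.8. The article states 20 per group, at which power for these proportions is about 17.6%. That is a separate matter. It bears on this point only because the proportions must belong to some named outcome.

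**Inputs for the multiplicity check.** k = 8 items in Questionnaire 2 (Table 3); per-test level 0.05 (Statistical analysis); 20 patients per group (Sample Size). It is assumed that the items are among the qualitative variables to be compared between groups.

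**Chance of at least one false positive, independent tests:** 1 − (1 − 0.05)^k.

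- Eight items, either direction: 1 − 0.95^8 = 0.337.
- Eight items, counting only results that favour Group B (half of each 0.05): 1 − 0.975^8 = 0.183.
- Eight items plus the total, treated as nine independent tests: 1 − 0.95^9 = 0.370. This overstates, because the total is built from the items.
- The two retention items only: 1 − 0.95² = 0.0975.
- One named primary: 0.05.
- Bonferroni over eight, 0.00625 each: 1 − 0.99375^8 = 0.049.

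**Allowing for correlation and discrete tests.** Eight three-level items were simulated with 20 per group and no true difference, 3,000 runs per setting. The assumptions, none of them from the article, were latent inter-item correlations of 0, 0.3, 0.5 and 0.7 and category probabilities of (1/3, 1/3, 1/3), (0.2, 0.3, 0.5) and (0.1, 0.2, 0.7). The tests were Pearson throughout, Fisher's exact throughout, or Fisher's only when an expected count fell below 5.

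- At least one of the eight items at p ≤ 0.05: 24.5% to 34.7%.
- With a t-test on the total added to the mixed Pearson/Fisher rule: 26% to 36%.

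The low end comes from skewed answers and high correlation, the high end from evenly spread, independent answers. Comparisons of Questionnaire 1 items and the before-after test are not counted, since neither compares the two adhesives after use.

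**Content of the Questionnaire 2 total, from Table 3.**

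- Items 1 and 2, hold of the upper and lower denture: 2/8 = 25%.
- Item 4, how long the adhesive worked: with it, hold is 3/8 = 37.5%.
- Item 3, chewing: 1/8.
- Items 5 to 8, taste, removal of the adhesive, cleaning the denture, cleaning the mouth: 4/8 = 50%.

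**The case against.** The strongest reply is that this is an article, and that an outcome hierarchy and a multiplicity procedure commonly sit in a full protocol or analysis plan that is not shown. That would answer a complaint about silence. The article is not silent, however: it fixes one threshold for all variables alongside a single stated aim, and as written the two do not fit together.

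It can also be said that the 0.05 sentence sits beside the description of age and qualitative characteristics and does not name the questionnaire items. That is fair, and the error rates above are therefore conditional. The items are categorical, though, and the sentence covers all qualitative variables, so the natural reading includes them.

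Four stronger readings are tempting, and the documents do not support them:

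- A reader might infer a one-in-three risk of wrongly favouring the essential-oil product. The 34% counts errors in both directions; the one-directional figure under independence is about 18%.
- A reader might say that taste, removal and cleaning dominate the total. They are exactly half of the items: the largest block, but not a majority.
- A reader might argue that better hold makes removal and cleaning harder, so the total would hide a retention benefit. The article gives no source for this. The study in its Discussion reports no significant gain in ease of removal, which is not a worsening.
- A reader might conclude that the total should be dropped. The Abstract and the Statistical analysis section present it as the measure of overall satisfaction, and the Methods say that Questionnaire 2 is meant to cover convenience. It can serve that purpose; what it cannot do is represent retention alone.

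**Conclusion.** The point holds. No comparison is tied to the stated aim, and following the text as written raises the chance of a false between-group finding well above 5%. For the eight Questionnaire 2 items it is 34% under independence and roughly 25–35% over the assumed correlations, answer distributions and choices of test. For a false result favouring the essential-oil arm it is about 18% under independence. These figures rest on all eight items being tested between groups at 0.05 with 20 per group and no true difference.

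The total cannot substitute for the retention aim, because only 25% of its items (37.5% with duration of hold) concern retention. This is a matter of content and needs no assumption about how the items move together.

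**What to change.** Before any data are seen:

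1. Name one retention comparison of Group A with Group B at day 7 as primary, at two-sided 0.05. Questionnaire 2 item 2 (lower denture) is one candidate, since the Abstract expects the gain there. Another retention item would serve if justified in advance.
2. State that the sample-size proportions 0.37 and 0.22 refer to that outcome, or restate them for it.
3. Make the other seven items and the total secondary, reported with effect sizes and 95% confidence intervals, and either Holm-adjusted or labelled exploratory. With Holm over these eight, the smallest p-value is compared with 0.05/8 = 0.00625.
4. Keep the total as a secondary measure of overall satisfaction, and report hold and chewing (items 1 to 4) separately from convenience (items 5 to 8).

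Steps 1, 3 and 4 change wording only and need no extra patients, visits or data. The price is that fewer results can be called significant. Step 2 needs the sponsor to say where the proportions come from, and may bring the sample-size discrepancy noted above into the open.

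### The before-after Wilcoxon test compares two questionnaires with different content, so the paired difference does not measure a change in satisfaction

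*Protocol article*

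**What the plan says.** The Method subsection plans sixteen closed questions in all: "eight during denture insertion without using denture adhesives and eight questions seven days after using denture adhesives". The first set is Table 2 (Questionnaire 1). The second is a separate form, Table 3 (Questionnaire 2), completed a week later.

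The Statistical analysis section then builds the outcome in three consecutive sentences:

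- The score is defined first: "The total of each questionnaire's scores will be used to determine the overall satisfaction with the results".
- A rescaling step follows, in which each patient in either group is given a satisfaction percentage.
- The test comes last: "The Wilcoxon signed-rank test will be used to compare patient satisfaction before and after the interview".

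No numeric coding of the answers is given, and the percentage is not defined. The abstract expects overall satisfaction to rise significantly with the essential-oil adhesive, and the Results section expects better overall comfort.

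**The concern.** A signed-rank test on paired data is informative about change only if the same quantity is measured twice. Here the first form asks about the denture and the second mostly about the adhesive. For example, Questionnaire 1 closes with "Do you have any issues with swallowing because of the denture", which is not asked again, and Questionnaire 2 includes "How does this denture adhesive taste", which has no baseline.

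At stake is the only before-after test in the article, and with it any statement that satisfaction improved from insertion to day 7. A significant result could arise because the day-7 questions are easier or harder to answer favourably. A real improvement could be hidden for the same reason. The loss cannot be repaired at analysis: an item not asked at day 7 has no after value.

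**Working it through.** **Step 1: item matching (Tables 2 and 3).**

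| Item | Questionnaire 1, insertion | Questionnaire 2, day 7 | Comparable? |
|---|---|---|---|
| 1 | Upper denture retention | Adhesive's hold on upper denture | Same topic and options, reworded |
| 2 | Lower denture retention | Adhesive's hold on lower denture | Same topic and options, reworded |
| 3 | Chewing, satisfaction level | Chewing, worse / no difference / better | Same topic, different scale |
| 4 | Comfort | Hours of action | No |
| 5 | Speech | Taste | No |
| 6 | Fit and removal of denture | Removal of adhesive | No, the object differs |
| 7 | Soft-tissue harm, Yes/No | Cleaning the denture | No |
| 8 | Swallowing problems, Yes/No | Cleaning the mouth | No |

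Three of eight topics are shared, and five of eight items on each form have no counterpart. Item 1 at insertion reads "To what extent do you find the retention of your upper denture satisfactory"; at day 7 the subject of the question is the adhesive. Item 3 at day 7 already asks for a change, so subtracting a baseline level from it has no clear meaning. On Questionnaire 1 items 7 and 8, Yes is the unfavourable answer, so a total needs reverse coding.

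**Step 2: expected difference with no change in satisfaction.** The article gives no figure to reproduce, so these inputs are assumptions: three-level items coded 1 to 3 and answered in equal thirds (mean 2), and Yes/No items coded 1 to 2 with 50% or 90% favourable answers (mean 1.5 or 1.9).

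- Questionnaire 1 total: 6 × 2 + 2 × 1.5 = 15.0 at 50%; 6 × 2 + 2 × 1.9 = 15.8 at 90%. Range 8 to 22.
- Questionnaire 2 total: 8 × 2 = 16.0. Range 8 to 24.
- Raw difference: +1.0 at 50%; +0.2 at 90%.
- Percent of maximum: 16/24 − 15/22 = 66.7 − 68.2 = −1.5 points at 50%; 66.7 − 71.8 = −5.1 points at 90%.
- Min-max percentage: 8/16 − 7/14 = 0 at 50%; 50.0 − 7.8/14 = 50.0 − 55.7 = −5.7 points at 90%.

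The apparent change can be positive, zero or negative, depending only on the scoring and on two items that are never repeated.

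**Step 3: rejection rate of the Wilcoxon test.** Simulation with 20 patients, within-person item correlation 0.3, no true change, and a nominal level of 5%:

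| Scoring | 50% favourable | 90% favourable |
|---|---|---|
| Raw totals | about 32% | 5–6% |
| Percent of maximum | 8% | 43–45% |
| Min-max percentage | 5% | 25–27% |

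**Step 4: content alone.** With min-max scores, which remove any range difference, and the five adhesive-only items shifted by half a latent standard deviation, rejection is about 70% in either direction (about +11 or −11 points).

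A second setup held the three shared answers identical before and after, with 30/40/30 answers on the other three-level items and 50% favourable on the Yes/No items. It rejected in 44% of trials on raw totals and 5% on rescaled totals. Moving the five adhesive-only items to 15/35/50 or 50/35/15 shifts the rescaled total by 5 × 0.35 / 16 = 10.9 points, and rejection is 85% in either direction.

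**The case against.** Several points on the other side are fair.

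- **Score ranges.** A reader might infer that the two totals have different ranges. The document does not establish this. The ranges 8–22 and 8–24 follow only from an assumed coding; scoring Yes/No at the ends of the three-level scale makes them equal, and the per-patient percentage may be meant to do so. The point must rest on content, which rescaling does not cure (Step 4).
- **False-positive rates.** It is tempting to cite 32% or 45% as the error rate of the plan. These are single cells of a table that also contains 5%. The answer distributions are not in the document, so only the range can be stated.
- **The test variable.** The Wilcoxon sentence refers only to satisfaction, and the totals and percentage come from the two sentences before it. That the test uses them is the natural reading but still an inference. An unseen full protocol might specify the variable and coding. It would not change the two printed forms.
- **The main comparison.** A reader might conclude that the comparison of the two adhesives fails. It does not, on this ground. The stated aim is to compare the adhesives, and both groups answer the same Questionnaire 2, so comparing it between groups is unaffected.
- **The retention items.** These might look like valid pairs. They share topic and options, but the day-7 wording asks about the adhesive, so they too are imperfect.

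**Conclusion.** The concern holds as a mismatch of content between the two forms. On the natural reading, the planned before-after test subtracts a rating of the denture from what is largely a rating of the adhesive. The result is not a change in one quantity and cannot support a claim that satisfaction rose from baseline. The expected gain in comfort cannot be examined from insertion to day 7 at all, because comfort is not asked at day 7; nor are speech, tissue harm or swallowing.

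The item matching needs no assumption. The numerical size does: about 5% to 45% rejection under no true change when three-level items are answered alike (20 patients, correlation 0.3, three scoring methods, 50% to 90% favourable Yes/No answers), and about 70% in either direction if the adhesive-only items are answered half a standard deviation better or worse. The fault is confined to the before-after analysis.

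**What to change.** 1. At the existing day-7 contact, repeat all eight Questionnaire 1 items with identical wording and response options.
2. Keep the adhesive-only items (duration, taste, removal, cleaning of denture and mouth) as a separate block, compared between groups only.
3. Run the Wilcoxon signed-rank test on the repeated items or their total.
4. Describe the contrast as insertion without adhesive versus after seven days of adhesive use, in place of before and after the interview.

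If the forms cannot change, drop the before-after test of totals. Report the two retention items before and after as exploratory only, and note the changed wording.

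Cost: up to eight more closed questions at a contact already planned, a form change that may need an ethics and registry amendment, and a one-line change to the analysis. It has to be made before day-7 data are collected, because the missing answers cannot be recovered afterwards.
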